##### Postpartum depression and anxiety

2.5.2.5

The Edinburgh Postpartum Depression Scale (EPDS) will be employed to assess depressive symptoms. The scale comprises 10 items, which will be administered after the final acupuncture session and again 6–8 weeks after delivery. Each item is graded on a four-point scale (0 to 3 points). A cumulative total score of ≥13 points indicates a diagnosis of postpartum depression.

#### Safety assessment

2.5.3

Common adverse reactions associated with acupuncture include incidents such as broken needles, localized hematoma, bleeding, infection, and localized severe sharp pain. Post-delivery, common adverse reactions encompass late postpartum hemorrhage, postpartum infection, and constipation. Any adverse events (AEs) occurring during the study period will be thoroughly assessed, treated, and documented in the case report form (CRF).

### Follow-up

2.6

#### Follow-up 1—6–8 weeks after delivery

2.6.1

Patients will undergo follow-up through outpatient visits. Urination sensations will be assessed using the Traditional Chinese Medicine Syndrome Quantification Scale, where:0 points: Unable to urinate;2 points: Dribbling out urine, with a sense of difficulty;4 points: Urination is acceptable, with a residual feeling;6 points: Very smooth, without any residual sensation.

#### Follow-up 2—1 year after delivery

2.6.2

Patients will be followed up via telephone. The assessment will include monitoring symptoms related to urination, defecation, and pelvic organ prolapse. Additionally, the Pelvic Floor Dysfunction Questionnaire (PFDI-20) will be administered.

We aim for ≥90% follow-up retention. The 6–8 week visit allows a ± 7-day window; the 1-year telephone follow-up allows ±30 days. Validated Chinese versions of EPDS and PFDI-20 will be administered by trained assessors.

### Data management and monitoring

2.7

Case Report Forms (CRFs) will be developed to document and store individual patient data. To streamline data management and process monitoring, an electronic CRF system based on the ResMan platform will be implemented. Following data entry and resolution of any queries by researchers to ensure accuracy, database locking will be performed by data managers. All hardcopy and electronic study documents will be archived for a minimum of 5 years after publication. Readers or reviewers with data inquiries may contact the corresponding author to request access to the original data.

An independent Data and Safety Monitoring Board (DSMB, composition detailed in Table 4) has been established to safeguard participant safety and ensure data integrity. Comprising independent experts free from financial conflicts of interest, the DSMB will:Conduct regular data reviews at six-month intervals;Perform an interim analysis when 50% enrollment (*n* = 330) is reached, focusing on cumulative safety data (adverse events) and conducting futility assessments;Provide confidential recommendations to the Trial Steering Committee regarding trial continuation, modification, or termination based on interim analysis findings.

**Table 4 tab4:** Data and Safety Monitoring Board (DSMB).

Member name	Affiliation	Roles and responsibilities
[name]	First Teaching Hospital of Tianjin University of TCM	Review the protocol with respect to ethical and safety standards. Review the progress of the trial.
[name]	First Teaching Hospital of Tianjin University of TCM	Monitor the safety of the trials. Review and interpret the data generated from the study.
[name]	First Teaching Hospital of Tianjin University of TCM	Adjudicate adverse events.

Prespecified trial stopping rules include: occurrence of ≥3 intervention-related serious adverse events (SAEs), or interim analysis indicating significant harm. All adverse events (AEs) and serious adverse events (SAEs) must be reported to both the DSMB and ethics committee within 24 h of documentation.

### Quality control

2.8

To ensure the trials’ quality, standardized training will be provided to all acupuncturists, obstetricians, evaluators, and statisticians before the official launch of the clinical trial. The training will encompass research goals and content, patient recruitment, treatment procedures, patient communication skills, and outcome evaluation, aiming to maintain consistency across various patients and researchers. This approach ensures the feasibility and safety of the clinical research. Throughout the clinical trial, independent monitors will regularly visit each center to verify strict adherence to the research plan. They will also scrutinize the original data to ensure the CRFs are accurate, complete, and correct.

### Sample size

2.9

This study employs a superiority design to evaluate the effect of electroacupuncture on the overall incidence of postpartum urinary retention (PUR), encompassing all subtypes (overt, covert, and persistent). Based on the research findings, the incidence of overt PUR in the intervention group is projected at 4.0%, while in the control group, it is estimated to be 9.0% based on previous observational data and a recent clinical trial in a similar population (4). The non-inferiority margin (*δ*) was set at 5%. Assuming a 1:1 ratio between the intervention and control groups, and utilizing a superiority test with a significance level (*α*) of 0.05, a power (1-*β*) of 80%, and accounting for a potential dropout rate of 10%, the study is planned to enroll 660 patients, evenly distributed with 330 in each group. The calculation formula is as follows:
$$n1=n2=[p_{1}(1-p_{1})+p_{2}(1-p_{2})]{\left(\frac{z_{1-\alpha }+z_{1-\beta }}{p_{1}-p_{2}-\delta }\right)}^{2}$$

While acknowledging that the initial effect size estimation was primarily informed by overt PUR data, we have implemented a comprehensive data collection system to capture all PUR subtypes, ensuring the primary outcome measure “PUR incidence” accurately reflects clinical reality. We anticipate this sample size will provide sufficient statistical power to detect clinically meaningful differences in overall PUR incidence across all subtypes. During final analysis, we will calibrate the effect size according to the actual observed incidence rates of all PUR subtypes, thereby ensuring proper alignment between the effect size and primary endpoint while enhancing the robustness and generalizability of our findings.

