## Introduction

1

Postpartum urinary retention (PUR) is a serious and common clinical complication after delivery (1), mainly manifested as voiding disorders or incomplete bladder emptying. Based on its different clinical manifestations, PUR can be classified into overt, covert, and persistent PUR. Overt PUR refers to the inability to void 6 or more hours after vaginal delivery or removal of catheter after cesarean section. Covert PUR is defined as post-void volume (PVR) of >150 mL measured by ultrasound or catheterization after spontaneous urination. Persistent PUR is urinary retention lasting beyond 3 days postpartum and requires indwelling catheter or intermittent self-catheterization (2, 3).

Based on differences in diagnostic criteria, measurement methods, and timing, the incidence of PUR varies from 1.5 to 45% (4). However, covert PUR is somewhat concealed, making clinical screening and management more challenging, and it is more prone to delayed diagnosis and misdiagnosis. Although some studies have shown that covert PUR can normalize within a few days, even a single over-distension of the bladder can cause long-term urination disturbance, affecting the long-term function of the bladder, leading to recurrent urinary tract infections, and even renal failure (5). Additionally, PUR can affect uterine involution, resulting in increased postpartum bleeding, which imposes a heavy psychological burden on the parturients and seriously impacts their physical and mental recovery, as well as their quality of life and long-term health (4). Therefore, early diagnosis and prevention of PUR are of great significance for the physical and mental well-being of parturients.

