#### Primary outcome

2.5.1

The primary outcome is the PUR incidence.

The incidence of postpartum urinary retention (PUR) will be evaluated in accordance with the following criteria, which are grounded in the diagnostic guidelines outlined in “Postpartum urinary retention: an expert review” published in the American Journal of Obstetrics and Gynecology.Overt PUR: Inability to void spontaneously within 6 h postpartum or within 6 h after removal of the indwelling catheter following cesarean section.Covert PUR: Post-void residual (PVR) urine volume ≥ 150 mL after spontaneous voiding.Persistent PUR: Requirement for an indwelling catheter or intermittent catheterization by the 3rd day postpartum.

Assessment time points are: the first urination after delivery, 6 h after delivery, the initial urination on the first day, and the second day following acupuncture. Meeting any of the aforementioned criteria at any assessment point will be considered as a positive PUR case.

The PVR of the bladder will be measured using an Ultrasonic Bladder Scanner (BVI-9400 BladderScan^®^, Verathon Medical Europe, Ijsselstein, The Netherlands). All BladderScan BVI-9400 devices will be calibrated annually according to the manufacturer’s guidelines. Operators must complete a standardized training program and pass a competency assessment before performing study measurements. To ensure accuracy, any PVR measurement ≥150 mL will be immediately rechecked by a second, blinded operator within 15 min. The average of the two readings will be recorded as the final PVR value. The recorded PVR of the bladder and whether catheterization was required will be documented. The specific measurement times are illustrated in Figure 3.

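### Section 2.9 derives its 80% power from overt PUR rates, but the primary outcome is any overt, covert or persistent PUR, so power for the primary endpoint is unsupported

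*Protocol article*

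**What the plan says.** Section 2.9 of the protocol article (Sample size) gives the target as "overall incidence of postpartum urinary retention (PUR), encompassing all subtypes (overt, covert, and persistent". The rates that follow concern one subtype: "the incidence of overt PUR in the intervention group is projected at 4.0%, while in the control group, it is estimated to be 9.0" per cent, the control figure being credited to earlier observational work and one recent trial. With alpha 0.05, 80% power, 1:1 allocation and 10% dropout, the section arrives at 330 per arm, 660 in total.

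Section 2.5.1 (Primary outcome) lists three definitions. The covert one is "Post-void residual (PVR) urine volume ≥ 150 mL after spontaneous voiding". The section names four assessment times and adds: "Meeting any of the aforementioned criteria at any assessment point will be considered as a positive PUR case".

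Section 2.9 concedes that the effect size came mainly from overt data. It expects power for overall PUR to be adequate, without a figure, and then says: "During final analysis, we will calibrate the effect size according to the actual observed incidence rates of all PUR subtypes".

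The Introduction says that, depending on criteria, measurement and timing, "the incidence of PUR varies from 1.5 to 45" per cent. Section 2.10 makes all tests two-sided at 0.05.

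**The concern.** A sample size calculation supports the endpoint whose rates went into it. Here the rates describe overt PUR, while the test will be run on a composite that adds covert PUR, detected by repeated bladder scans, and persistent PUR. The composite control rate cannot be lower than the overt rate and may be much higher. The effect on the composite depends on how far electroacupuncture reduces covert PUR, about which the plan assumes nothing.

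At stake is how the result will be read. A reader of a null result would take from section 2.9 that the trial had an 80% chance of finding the effect of interest on overall PUR, and nothing in the document supports that. The calibration sentence looks like the remedy, but it takes effect at final analysis, when the sample size is already fixed.

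**Working it through.** **1. Reproduce 330 per arm.** Inputs from section 2.9: p1 = 0.04, p2 = 0.09, power 80%, dropout 10%. The printed formula, with the margin set to 0 and its one-sided z:

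- p1(1−p1) + p2(1−p2) = 0.0384 + 0.0819 = 0.1203
- n = 0.1203 × ((1.645 + 0.842)/0.05)² = 297.5, so 298 per arm
- 298/0.9 = 332 per arm after dropout, close to 330. The pooled-variance version gives 300, and 300 × 1.1 = 330.

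A two-sided calculation gives 378 per arm, or 420 after dropout, which does not match. Inserting the stated 5% margin gives 75 per arm or a zero denominator, depending on which arm is p1. So 330 is the answer for overt PUR, one-sided, with no margin.

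**2. Reference power for overt PUR under the planned two-sided testing.** Evaluable n = 330 × 0.9 = 297 per arm. Formula for this and all later figures:

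power = Φ[(d − 1.96·se0)/se1], with se0 = √(2p̄(1−p̄)/n) and se1 = √((p1(1−p1) + p2(1−p2))/n).

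For 4% vs 9%, power is 70% with 297 per arm and 74% with 330. One-sided with 297 it is 80%. About ten points of any shortfall from 80% at the overt rates therefore come from sidedness and not from the composite.

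**3. Power for the composite.** The document gives no composite rates. The control rates below are assumptions lying within the Introduction's 1.5% to 45% range. Worked example, 20% vs 15%, n = 297: p̄ = 0.175, se0 = 0.0312, se1 = 0.0311, (0.05 − 0.0611)/0.0311 = −0.36, power 36%.

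| Assumed effect (two-sided 0.05, 297 per arm) | Control 15% | 20% | 30% | 45% |
|---|---|---|---|---|
| 5-point fall | 45% | 36% | 28% | 23% |
| RR 0.80 | 19% | 24% | 38% | 61% |
| RR 0.44 (4/9, the overt effect) | 91% | 97% | >99% | >99% |

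With one-sided testing, the first row would be 58%, 48%, 39% and 34%.

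**4. Overt effect achieved, covert PUR unaffected.** Assume that 10% of women without overt PUR have covert PUR in both arms:

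- control: 0.09 + 0.91 × 0.10 = 18.1%
- electroacupuncture: 0.04 + 0.96 × 0.10 = 13.6%
- power 32% with 297 per arm, 35% with 330

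**5. Composite reduction detectable with 80% power, two-sided.**

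| Per arm | Control 20% | 30% | 45% |
|---|---|---|---|
| 297 | 8.4 points | 9.9 | 11.2 |
| 330 | 8.0 points | 9.5 | 10.7 |

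**The case against.** The protocol discloses the mismatch openly. A composite also has more events: if covert PUR falls by the same proportion as overt PUR, power is above 90% at every control rate considered. The 45% control rate is the top of a literature range and not a forecast for primiparous women planning vaginal delivery. Part of the shortfall comes from one-sided sizing. And since the intention-to-treat analysis keeps all randomised women, with multiple imputation, 330 per arm may be a fairer basis than 297.

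Most of this stands as a limit on the size of the point. The scenarios are assumptions and do not bound the power; the 70% reference separates out the sidedness effect; and using 330 raises the 5-point figures only to 49%, 39%, 30% and 25%. It does not supply what is missing. Disclosure followed by an unquantified expectation is not a power statement, and nowhere does the document state or justify an equal relative effect on covert PUR.

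A reader might also take the calibration sentence as a plan to redefine the target effect from the data, or to reinterpret a null result. The text does not go that far. Section 2.10 separately fixes an intention-to-treat analysis, a relative risk with 95% confidence interval and a two-sided 0.05 level, none of which uses the planning effect. The fair criticism is that the sentence is undefined and cannot change a power already set by the sample size and the true rates.

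**Conclusion.** The point holds: the 80% power in section 2.9 belongs to overt PUR at 4% vs 9%, one-sided, and not to the primary endpoint. Even for overt PUR, two-sided power is only about 70% with 297 per arm. For the composite, the scenarios tried give anything from 19% to over 99%, depending mainly on the unstated effect on covert PUR. These figures rest on assumed composite rates and effects, 297 evaluable per arm and a normal approximation.

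A reader might infer that the trial is underpowered. The document does not support that, because the favourable scenario is not excluded. What it supports is that power for the primary endpoint is unsupported.

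**What to change.** In section 2.9:

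- Label 4% vs 9%, and the power attached to it, as applying to overt PUR only.
- Replace the expectation of adequate power with two-sided power for the composite over stated assumed control rates and effects, together with the 80%-power detectable difference at the planned size (step 5 of the working).
- Delete the calibration sentence. State that the prespecified test of the composite, with its estimate and confidence interval, is the sole basis for the primary conclusion.

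Naming overt PUR as a key secondary endpoint is optional.

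The cost is wording, and a stated power that becomes conditional and less favourable. No extra patients are needed.

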### Statistical analysis

2.10

Demographic characteristics, general situations, and baseline conditions of the two groups will be compared and analyzed. For measurement data, an independent samples t-test or Wilcoxon rank-sum test will be employed, while χ^2^ test or Fisher test will be used for categorical data.

The incidence of PUR will be accurately assessed using Fisher’s exact test, and the relative risk (RR) along with the corresponding 95% confidence interval will be calculated. For other ordinal data, the Wilcoxon rank-sum test will be applied, while clinical counting data will undergo testing through the χ2 test. Postpartum depression and anxiety will be compared using Fisher’s exact test, and the RR along with the corresponding 95% confidence interval will be computed. Subject blinding effectiveness will be analyzed using the James Blinding Index. All statistical tests will be two-sided, and a *p* value less than 0.05 will be considered statistically significant for the tested differences.

For exploratory subgroup analysis, participants will be stratified into different subgroups based on age (< 40 years, ≥ 40 years), BMI (< 25 kg/m^2^, ≥ 25 kg/m^2^), duration of labor (< 700 min, ≥ 700 min), epidural anesthesia (with or without), vaginal midwifery techniques (forceps midwifery, fetal head attraction midwifery, fetal head rotation, perineotomy), gestational age (> 280 days, ≤ 280 days), and newborn birth weight (< 4,000 g, ≥ 4,000 g). The incidence difference between the two groups will be compared within each subgroup using the same statistical methods as mentioned above.

The primary analysis will follow the intention-to-treat (ITT) principle. Missing data will be handled using multiple imputation. A logistic regression model adjusting for study center will be used for the primary outcome. Secondary and subgroup analyses will apply Bonferroni correction for multiple comparisons.

GraphPad Prism 10.2 will be used for all statistical analysis.

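### The 330 per arm rests on a one-sided 5% level, but the tests are two-sided: power is about 70%, not 80%, and the stated 5% margin has no place in the calculation

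*Protocol article*

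**What the plan says.** Section 2.9 (Sample size) of the protocol article opens: "This study employs a superiority design to evaluate the effect of electroacupuncture". Its planning rates are for overt retention: "the incidence of overt PUR in the intervention group is projected at 4.0" per cent, and "while in the control group, it is estimated to be 9.0" per cent. It then states: "The non-inferiority margin (*δ*) was set at 5" per cent. It continues with "utilizing a superiority test with a significance level" of 0.05, 80% power and 1:1 allocation, and concludes, "accounting for a potential dropout rate of 10%, the study is planned to enroll 660 patients, evenly distributed with 330 in each group".

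The formula printed below this text multiplies the sum of the two binomial variances by the square of (z(1−α) + z(1−β)) / (p1 − p2 − δ).

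Section 2.10 (Statistical analysis) says "All statistical tests will be two-sided", with significance at p below 0.05. It names Fisher's exact test with a relative risk and 95% confidence interval for retention incidence. Further down it also names a centre-adjusted logistic model for the primary outcome.

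**The concern.** Two things in section 2.9 do not fit the rest of the plan.

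- **Sidedness.** The formula takes z(1−α) at α = 0.05, which is 1.645. A two-sided 5% test needs z(1−α/2), which is 1.960. A sample size built on the first is too small for the second.
- **Margin.** A superiority test against no difference has no non-inferiority margin. The one given, 5 points, equals the whole assumed effect (9% − 4%), so entering it in the formula cannot produce the stated sample size.

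The first error means the trial lacks the power it claims, and a null result would be read as coming from an 80%-powered trial. The second makes the calculation impossible to reproduce from its own inputs. It also leaves section 2.9 open to three readings of the hypothesis: superiority over zero, superiority by 5 points, or non-inferiority. The futility assessment planned at 330 enrolled (section 2.7) also needs one clear hypothesis.

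**Working it through.** **Inputs.** From section 2.9: p1 = 0.04, p2 = 0.09, α = 0.05, power 0.80, δ = 0.05, dropout 10%, 330 per arm. From section 2.10: two-sided tests at 0.05.

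Variance term: V = 0.04 × 0.96 + 0.09 × 0.91 = 0.0384 + 0.0819 = 0.1203.

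**Step 1. The formula as printed, δ = 0.05, one-sided quantile.** (1.645 + 0.842)² = 6.183.

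- Denominator 0.04 − 0.09 − 0.05 = −0.10: n = 0.1203 × 6.183 / 0.01 = 74.4, so 75 evaluable per arm. With 10% dropout, 74.4 / 0.9 = 82.6, so 83 enrolled.
- Denominator 0.09 − 0.04 − 0.05 = 0: n is undefined.

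Neither is 330.

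**Step 2. Reproducing 330.** Set δ = 0 and keep the one-sided quantile: n = 0.1203 × 6.183 / 0.0025 = 297.5, and 297.5 / 0.9 = 330.6. A pooled-variance version, also one-sided, gives 300, and 300 × 1.1 = 330. Of the versions tried (pooled and unpooled, with and without continuity correction), only one-sided ones without the correction match.

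**Step 3. The two-sided requirement.** (1.960 + 0.842)² = 7.849. n = 0.1203 × 7.849 / 0.0025 = 377.7, so 378 evaluable per arm. 377.7 / 0.9 = 419.7, so 420 enrolled per arm, 840 in total. The pooled version gives 381 evaluable and 424 enrolled.

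**Step 4. Two-sided power of the planned trial.** After 10% loss, 330 × 0.9 = 297 per arm. The standard error is √(0.1203 / 297) = 0.02013, and 0.05 / 0.02013 = 2.484. Power is Φ(2.484 − 1.960) = Φ(0.524) = 0.70. With the one-sided quantile it is Φ(2.484 − 1.645) = Φ(0.839) = 0.80, the protocol's figure.

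Exact powers were found by enumerating both binomial distributions at 4% and 9%:

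| Two-sided test at 0.05 | 297 per arm | 330 per arm |
|---|---|---|
| Normal approximation, unpooled | 70.0% | 74.5% |
| Normal approximation, pooled | 69.6% | 74.2% |
| Pearson, exact enumeration | 71.3% | 75.3% |
| Fisher, exact enumeration | 64.5% | 69.8% |

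For 80% power with Fisher's test, 405 evaluable per arm gives 79.9% and 410 gives 80.4%. At 410 evaluable, 410 / 0.9 = 455.6, so about 456 enrolled per arm.

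**The case against.** The core is hard to dispute, but five qualifications deserve an answer.

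- **The 70% belongs to 297 evaluable per arm, not 330.** Correct. The protocol's 80% is on the same post-dropout basis, so 297 is the fair comparison. Analysing all 330 still leaves power at 74–75%. Multiple imputation keeps everyone in the analysis but does not by itself restore the lost information.
- **The margin does not cause the shortfall.** Also correct. The power loss comes entirely from the one-sided quantile. The margin is a separate error affecting reproducibility and the statement of the hypothesis.
- **The 64% depends on which test is primary.** It does, because section 2.10 also names a centre-adjusted logistic model. The 70% does not depend on Fisher's test, and the two-sided rule covers all tests.
- **The analysis criterion is really clear.** Section 2.10 uses no margin and fixes a two-sided test of difference, so superiority over zero is the most natural reading. Section 2.9 still sets a margin and writes it into its formula, and should not.
- **The planning rates are for overt retention, while the endpoint covers all subtypes.** This is a separate weakness that the protocol partly acknowledges. It means 70% is the power at the stated rates, not necessarily for the composite. As an illustration with an assumed composite control rate of 15%, two-sided power at 297 per arm would be about 45% for the same 5-point difference, or about 91% for the same relative risk. The protocol gives no composite rates, so its 80% also rests only on 4% against 9%.

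**Conclusion.** The concern holds, and section 2.9 must be corrected. The planned size follows from a one-sided 5% level with no margin, which contradicts both the two-sided testing in section 2.10 and the 5-point margin in section 2.9 itself. At the protocol's own rates and 10% loss, two-sided power is about 70% (about 64% if Fisher's exact test is the primary test). The type II error is therefore about 30–36%, against the 20% implied. These figures assume event rates of 4% and 9%, 1:1 allocation and 297 evaluable per arm, and make no allowance for centre adjustment. The type I error of the planned two-sided test is not affected.

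**What to change.** In section 2.9:

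1. Delete the non-inferiority margin from the text and δ from the formula.
2. Replace z(1−α) with z(1−α/2).
3. State one hypothesis: superiority of electroacupuncture over sham, tested two-sided at α = 0.05.
4. Keep 660 patients and restate the power as about 70% for 9% against 4% with 10% loss, or about 64% if Fisher's exact test stays as the primary test. Say that these are the overt-retention rates.

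The cost is a rewording of one section and a less favourable stated power, with no extra patients. If the sponsor wants to keep 80%, the alternative is about 420 enrolled per arm (840 in total), or about 456 per arm (912 in total) with Fisher's test.
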